### Blinding

Outcome assessors, the principal investigator, and the study statistician will remain blinded to group allocation until database lock. Randomisation will be executed centrally through the secure REDCap system. Group-specific content within the digital platforms will be activated and managed by an unblinded administrator who has no role in outcome assessment, intervention supervision, data cleaning, or statistical analysis.

Because of the nature of non-pharmacological digital exercise interventions, complete blinding of participants and treating physiotherapists is not feasible. To minimise performance bias and expectancy effects, the study employs an active comparator (sham digital experience). Participants in the control arm will access a visually identical platform interface that provides general fibromyalgia self-management education and non-specific physical activity guidance, but without the active components (AI-driven real-time biomechanical feedback and structured PNE modules).

Participants will be informed that the trial compares two digital health management approaches, without disclosing any superiority hypothesis related to the AI/PNE intervention. They will be instructed not to reveal their perceived group allocation during outcome assessments. Technical support staff and adherence monitors will not be involved in outcome data collection.

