### AI-guided exercise with computer vision

Participants will complete three home-based sessions per week (30–40 minutes each) via a digital platform integrating artificial intelligence and computer vision (https://rehbody.net/) Rehbody is a clinically validated telerehabilitation platform that uses the participant’s device camera to capture and analyse movement patterns through AI-driven motion tracking. The system identifies joint angles, range of motion, and posture deviations in real time, providing immediate audiovisual feedback to ensure correct technique and prevent injury. It automatically adjusts exercise difficulty based on individual performance metrics and adherence data. All data are encrypted and stored on secure servers compliant with international data protection standards (GDPR). The program follows four progressive phases: adaptation (weeks 1–3), progression (weeks 4–6), consolidation (weeks 7–9), and maintenance (weeks 10–12) [16,18]. Exercises evolve from sit-to-stand with chair support and unweighted deadlifts to glute bridges, incline push-ups, and loaded Romanian deadlifts (S2 Appendix). All sessions are remotely supervised by a licensed physiotherapist who reviews adherence reports and responds to alerts [18,23].

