### Pain neuroscience education (PNE)

In parallel, Concurrently, participants will complete one asynchronous online module per week (https://proyectofibrobrain.org). The 12 sequential modules, adapted from validated frameworks [13,14,24], address topics such as nociplastic pain, central sensitisation, neuroplasticity, and psychosocial modulators [15,24,25]. Content incorporates multimedia resources, clinical metaphors (e.g., the “alarm system”), and guided reflection activities. Each module concludes with comprehension questions and self-assessment exercises to reinforce learning [26,27]. The modules were co-designed with patients with FM to ensure linguistic, cultural, and contextual relevance [13].

**Control group**Control participants will receive enhanced usual care according to clinical guidelines [3,8,9], typically including analgesics (paracetamol, tramadol), antidepressants (amitriptyline, duloxetine), anticonvulsants (pregabalin, gabapentin), and general lifestyle advice. In addition, they will use the same digital platforms with a visually identical interface and will receive standard, non-specific educational materials on fibromyalgia self-management and general physical activity guidance (without AI-guided exercise feedback or pain neuroscience education modules). Concomitant care will be documented systematically.

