### Intervention fidelity and adherence monitoring

All physiotherapists will complete a standardized training program and adhere to a detailed intervention manual specifying session structure, therapeutic content, and delivery protocols. Intervention fidelity will be evaluated monthly by an independent investigator uninvolved in intervention delivery. Audits will include digital log reviews (frequency, duration, accuracy), random checks of therapist documentation, and verification of protocol compliance.

Protocol adherence will be deemed satisfactory when ≥90% of planned components are delivered as outlined in the manual. Identified deviations will trigger corrective actions such as targeted feedback, refresher training, and additional supervision until compliance is restored. Fidelity indicators—including adherence rates, frequency of deviations, and corrective measures—will be summarised descriptively and reported in the Results section to document intervention integrity [38].

Participant adherence will be monitored automatically through the digital platforms. Participants will be considered adherent if they complete ≥80% of prescribed sessions (≥29/36 exercise sessions and ≥10/12 PNE modules). Automated SMS or email reminders will be issued for missed sessions, and non-adherent participants will receive motivational follow-up from the research team to address barriers.

Control group participants’ engagement (login frequency, material access, and time spent on the platform) will be monitored equivalently to ensure comparable exposure time. Study staff will conduct monthly check-ins to verify participation and reduce attrition bias across groups.

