### Data analysis

Analyses will follow both intention-to-treat (ITT) and per-protocol (PP) principles, consistent with CONSORT recommendations [21]. The ITT population will include all randomised participants, analysed according to their allocated group. Missing outcome data will be addressed using multiple imputation, assuming data are missing at random. Sensitivity analyses using last observation carried forward (LOCF) and complete-case approaches will be performed to assess the robustness of the findings.

The PP population will include participants who complete at least 80% of the prescribed intervention dose (≥29/36 exercise sessions and ≥10/12 PNE modules) and have no major protocol deviations. Baseline characteristics will be summarised descriptively and compared between groups using parametric (independent t-test) or non-parametric (Mann–Whitney U test) methods, depending on normality assessed via the Shapiro–Wilk test.

The primary analysis will evaluate the change in pain intensity (VAS, 0–10 cm) from baseline to week 13 (±7 days) between groups using both independent t-tests and Mann–Whitney U tests to ensure consistency of results. The anticipated effect size (Cohen’s d ≈ 0.65) was derived from prior trials of multidisciplinary and digital interventions in fibromyalgia, which reported moderate-to-large effects on pain reduction (range 0.5–0.7) [28,36,37]. Within-group changes will be assessed using paired t-tests or Wilcoxon signed-rank tests, as appropriate. Effect sizes (Cohen’s d) with 95% confidence intervals will be reported and interpreted using conventional thresholds [38].

Secondary outcomes (FIQ-R, 30-Second Sit-to-Stand, EQ-5D, NRS-Anxiety, adherence barriers) will be analysed using similar methods. Minimal clinically important differences (MCIDs) will be defined a priori as follows: 14% for FIQ-R total score, ≥ 2 repetitions for the 30-Second Sit-to-Stand, and ≥0.07 for EQ-5D index, based on previous validation studies. For repeated measures, mixed-effects models will account for within-subject correlations and time effects [39,40]. Multivariable regression analyses will adjust for relevant covariates (e.g., baseline pain, age, pharmacological treatment).

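### The per-protocol dose criterion counts PNE modules that controls never receive, so the set has either no controls or an adherence filter on one arm only

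*Protocol article*

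**What the plan says.** The protocol article's Data analysis section plans both an ITT and a per-protocol analysis. The per-protocol rule reads: "The PP population will include participants who complete at least 80% of the prescribed intervention dose (≥29/36 exercise sessions and ≥10/12 PNE modules"). The same sentence adds a second condition, "and have no major protocol deviations". The rule names no arm.

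The counts repeat the adherence definition under Intervention fidelity and adherence monitoring: "Participants will be considered adherent if they complete ≥80% of prescribed sessions (≥29/36 exercise sessions and ≥10/12 PNE modules").

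Both doses belong to the intervention arm. For exercise, "Participants will complete three home-based sessions per week (30–40 minutes each) via a digital platform"; for education, "participants will complete one asynchronous online module per week".

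The control-group paragraph says controls use the same platforms "without AI-guided exercise feedback or pain neuroscience education modules". The Blinding section says the control interface comes "without the active components (AI-driven real-time biomechanical feedback and structured PNE modules").

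For controls the article adds only that "Control group participants’ engagement (login frequency, material access, and time spent on the platform) will be monitored equivalently". It gives no threshold and no link to the per-protocol set.

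The Abstract names ITT alone as the analysis framework. The sentence in Data analysis that introduces the primary analysis does not say which population it uses.

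**The concern.** A per-protocol set is useful only if membership can be decided in both arms. Here the dose condition is written in units that exist in one arm. Either the analysis cannot be run, or someone must decide later how the rule treats controls.

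The obvious later decision is to apply the dose condition to the intervention arm and keep the controls. That selects on behaviour after randomisation in one arm only. The article itself gives reasons why completing sessions may be related to outcome: sessions may be suspended for moderate adverse symptoms, the platforms flag sessions left incomplete because of symptoms, and deterioration is a ground for discontinuing. An intervention participant who worsens may drop below 29 sessions and leave the set, while a control who worsens stays in. A difference from such a comparison cannot be read as a treatment effect, and nothing in Data analysis places it below the ITT result.

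**Working it through.** **1. Reproduce the thresholds.** Three sessions a week for 12 weeks is 36, and 0.80 × 36 = 28.8, rounded up to 29. One module a week for 12 weeks is 12, and 0.80 × 12 = 9.6, rounded up to 10. Both stated counts are correct.

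**2. Apply the rule literally.** The two counts are joined by 'and', so failing either one excludes a participant. A control completes 0 of 12 PNE modules, and 0 < 10. The per-protocol control group is therefore 0 of 25. The PNE count alone settles this, whatever one makes of the general activity guidance that controls receive.

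**3. Apply it to the intervention arm only.** Controls stay at 25 less any with a major deviation. The intervention arm shrinks to its adherers: at an assumed 60% or 80% adherence, 15 or 20 of 25.

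**4. Bias under no treatment effect.** Assume that adherence follows a normal propensity with correlation ρ to pain improvement, and that the top share p of the arm adheres. The expected spurious benefit is

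bias = ρ × SD × φ(c)/p, with c the (1 − p) normal quantile and φ the normal density.

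The SD is 3.0 cm (Sample size section). ρ and p are assumptions; the article gives neither. φ(c)/p is 0.644, 0.497 and 0.350 for p = 0.6, 0.7 and 0.8.

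| ρ | p | Bias (cm) |
|---|---|---|
| 0.1 | 0.8 | 0.1 × 3.0 × 0.350 = 0.10 |
| 0.1 | 0.6 | 0.1 × 3.0 × 0.644 = 0.19 |
| 0.3 | 0.7 | 0.3 × 3.0 × 0.497 = 0.45 |
| 0.5 | 0.8 | 0.5 × 3.0 × 0.350 = 0.52 |
| 0.5 | 0.6 | 0.5 × 3.0 × 0.644 = 0.97 |

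The range is about 0.1 to 1.0 cm, against the 2.0 cm difference used for the sample size. Simulating the same model (25 randomised per arm, t-test, nominal 5%) gives a type I error of about 5% at ρ = 0.1 and p = 0.8, 7 to 8% at ρ = 0.3 and p = 0.7, and 16% at ρ = 0.5 and p = 0.6.

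**5. The sign can reverse.** Suppose instead that adherence depends only on low baseline pain, with correlation r in size. Let baseline and follow-up pain have equal variance and correlation q. Participants with low baseline pain improve less through regression to the mean, and the correlation of adherence with worsening is r × √((1 − q)/2). At p = 0.7 and a change SD of 3.0 cm:

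- r = 0.3, q = 0.5: 0.3 × 0.500 × 3.0 × 0.497 = 0.22 cm against the intervention.
- r = 0.5, q = 0.3: 0.5 × 0.592 × 3.0 × 0.497 = 0.44 cm against the intervention.

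r and q are also assumptions.

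**The case against.** **The literal reading is strained, and the rest is detail.** A prescribed dose naturally refers to those who were prescribed it, so an empty control group is surely not intended. That is fair. But this reading leads straight to the one-arm filter. The article fixes a rule that fails on either reading, which is different from leaving a detail to a fuller document.

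**The per-protocol definition is not wholly one-sided.** This stands. The deviation condition covers both arms; starting outside structured therapy, for example, is a deviation in either group. Only the dose condition is one-sided.

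**Controls could be given a threshold.** A reader might infer that none is possible. The article does not support that: control logins, material access and time on the platform are recorded, and a cut-off could be built from them. None is stated, however, and selecting each arm on a different behaviour would not in itself restore comparability.

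**Per-protocol may show benefit even if the programme does nothing.** This is a tempting stronger reading, but the article gives no relation between adherence and pain change. The favourable sign is an assumption, step 5 shows that the opposite is possible, and at low correlation or high adherence the bias is small.

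**Per-protocol has equal standing with ITT, or would be used as a rescue.** This too goes further than the text. The article never makes per-protocol confirmatory, and the Abstract names ITT. What stands is that Data analysis does not rank the two.

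**Conclusion.** The point holds for the dose condition of the per-protocol definition and should be fixed. As written, the set contains no controls. If the condition is applied to the intervention arm alone, the comparison is no longer protected by randomisation. Its bias is unknown in size and sign: about 0.1 to 1.0 cm in favour of the programme if adherence correlates 0.1 to 0.5 with improvement and 60 to 80% adhere, and about 0.2 to 0.4 cm against it in the baseline-pain scenarios examined. All of these rest on assumed correlations and adherence shares and on the article's SD of 3.0 cm.

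The defect does not touch the ITT comparison, which includes everyone randomised by allocated arm. It is therefore not a threat to the trial's main result, provided ITT is clearly the primary analysis.

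**What to change.** 1. State in Data analysis that ITT is the primary population for the VAS comparison and that per-protocol is supportive only.
2. Remove the session and module counts from the per-protocol definition. Define the set by criteria that can be judged in both arms: eligibility violations, prohibited co-interventions, and assessment outside the Week 13 ± 7 day window. The counts can stay as a descriptive adherence measure in the intervention arm.
3. If an adherence-based effect is wanted, report it as supplementary. One option is a complier-average causal effect, with randomisation as the instrument, adherence at the stated cut as treatment received, and controls counted as untreated. State that a binary cut assumes no effect below it. If a participant below the cut gets a fraction f of the benefit and a share a adheres, the estimate is inflated by 1 + f(1 − a)/a: 1.13 times at a = 0.8, f = 0.5, and 1.53 times at a = 0.6, f = 0.8 (both assumed). State also that its confidence interval is wider than that of the naive per-protocol estimate.

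The cost is a few sentences of analysis text and, if item 3 is taken up, a short two-stage least squares run. No design change or new data are needed. The article says that no one had been recruited at submission; changes to the analytical strategy go through its own amendment process (ethics review and registry update).

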### Randomisation and allocation concealment

Randomisation will be performed using a computer-generated sequence with a 1:1 allocation ratio, employing permuted blocks of variable size (4–8 participants) to reduce allocation predictability. To minimise selection bias, randomisation will be stratified by age (<50 vs ≥ 50 years), given the established influence of age on FM outcomes.

Allocation concealment will be maintained through a centralised, web-based system (REDCap, Vanderbilt University), operated by an independent researcher not involved in intervention delivery or outcome assessment. This system provides automatic participant assignment with timestamped allocation records, ensuring transparency and traceability.

If web-based randomisation is unavailable, a validated contingency procedure will be implemented using sequentially numbered, opaque, sealed envelopes (SNOSE) prepared off-site by an independent statistician. Envelopes will be tamper-proof, opaque, and opened sequentially only after participant enrolment and baseline assessment.

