### Primary outcome

The primary endpoint is change in pain intensity (VAS) between baseline (week 0) and post‑intervention at week 13 (±7 days), immediately after completion of the 12‑week programme. Secondary endpoints will be assessed at the same timepoints [29]. Pain intensity was chosen as the primary outcome because it is the cardinal symptom of FM and the most consistently recommended endpoint in chronic pain trials [28].

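### The primary test of VAS change adjusts for neither baseline pain nor the age stratum, and so gives up precision that a 50-patient trial needs

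*Protocol article*

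**What the plan says.** Under Data analysis, "The primary analysis will evaluate the change in pain intensity" from baseline to week 13 between groups, "using both independent t-tests and Mann–Whitney U tests to ensure consistency of results". Neither test takes a covariate. The Sample size section sizes the trial on the same independent t-test.

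Under Randomisation and allocation concealment, "randomisation will be stratified by age", split at 50 years, "given the established influence of age on FM outcomes".

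Later in Data analysis, after the secondary outcomes and a remark on mixed-effects models for repeated measures, the protocol adds: "Multivariable regression analyses will adjust for relevant covariates". Baseline pain, age and drug treatment follow as examples. The sentence names no outcome, fixes no covariate list and does not say whether the result is primary, supportive or exploratory. Apart from this, baseline pain and age appear in the analysis only as subgroup factors.

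**The concern.** The protocol calls age prognostic and restricts randomisation on it, then leaves it out of the main comparison. If age does predict outcome, the unadjusted standard error is too large and the test is conservative.

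Baseline VAS is measured on everyone and is normally among the best predictors of follow-up VAS, but the plan uses it only by subtraction. Subtraction treats the slope of week-13 pain on baseline pain as 1. With equal variances at the two visits the slope equals the correlation, which is below 1. The change score therefore over-corrects: the group that starts higher by chance tends to improve more through regression to the mean. Baseline pain is not a stratification factor, so nothing in the design limits such an imbalance.

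At stake are precision in a trial with little to spare, and a primary estimate that moves with a chance difference at baseline.

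**Working it through.** **Inputs from the protocol.** Difference 2.0 cm, SD 3.0 cm, 25 per group, two-sided α = 0.05, about 10% attrition. The Sample size section does not say whether 3.0 cm is the SD of the change or of a single score, so both readings are shown.

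**Assumed.** Correlation r between baseline and week-13 VAS, which the protocol does not give, over 0.3 to 0.8; equal variances at the two visits.

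**Step 1: the planned test.** The standardised difference is 2.0/3.0 = 0.667. The noncentrality is 0.667 × √(25×25/50) = 2.357 on 48 degrees of freedom. Two-sided power from the noncentral t distribution is 63.7% (61.5% at the rounded d of 0.65). The stated 80% is not reproduced. With 45 completers (23 and 22) power is 58.9%.

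**Step 2: what adjustment does to the variance.** Let s be the SD of a single score.

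- SD of the change: s√(2(1−r))
- Residual SD after ANCOVA on baseline: s√(1−r²)
- Ratio of variances, ANCOVA to change: (1−r²)/(2(1−r)) = (1+r)/2

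The ratio is below 1 for any r below 1. The variance falls by (1−r)/2: 35% at r = 0.3, 25% at 0.5 and 15% at 0.7.

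**Step 3: power with 3.0 cm as the SD of the change.** Two further degrees of freedom are charged, for baseline and age stratum. The t-test stays at 63.7% whatever r is.

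| r | Residual SD (cm) | ANCOVA, 25/25 | ANCOVA, 23/22 |
|---|---|---|---|
| 0.3 | 2.42 | 81.6% | 77.3% |
| 0.5 | 2.60 | 75.9% | 71.2% |
| 0.7 | 2.77 | 70.6% | 65.8% |
| 0.8 | 2.85 | 68.2% | 63.3% |

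For example, at r = 0.5 the residual SD is 3.0 × √0.75 = 2.60, the standardised difference is 2.0/2.60 = 0.770, and the noncentrality is 0.770 × 3.536 = 2.72 on 46 degrees of freedom. Simulation with baseline and age stratum in the model gives about 81%, 75% and 69% at r = 0.3, 0.5 and 0.7. The formula is therefore optimistic by about one point, because it omits the cost of estimating the baseline slope.

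**Step 4: power with 3.0 cm as the SD of a single score, 25/25.**

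| r | t-test on change | ANCOVA |
|---|---|---|
| 0.3 | 49.7% | 67.7% |
| 0.5 | 63.7% | 75.9% |
| 0.7 | 84.6% | 89.8% |
| 0.8 | 95.5% | 97.0% |

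**Step 5: chance imbalance in baseline pain.** Take a single-score SD of 3.0 cm. The standard error of the baseline difference is 3.0 × √(2/25) = 0.85 cm. A gap of 1 cm or more in either direction is a deviation of 1/0.85 = 1.18 standard errors, which occurs in about 24% of such trials. Given a gap D, the change-score estimate shifts by (1−r)D. For D = 1 cm that is 0.7, 0.5 or 0.3 cm at r = 0.3, 0.5 or 0.7. The middle value is a quarter of the 2.0 cm target difference.

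Any gain from the age stratum cannot be computed from the protocol and is not counted.

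**The case against.** The planned t-test is valid. It is unbiased over repeated randomisation, it holds its type I error after stratified randomisation, and it matches both the endpoint and the sample size method. A change score does use baseline, by subtraction. The adjusted regression is already planned, with baseline pain and age as its first two examples, and its details could sit in an analysis plan that is not shown. The size of the gain rests on an unknown correlation and an ambiguous SD: with a single-score SD of 3.0 cm and r of 0.7 to 0.8 it is only 1.5 to 5 points. Conversely, an SD of change of 3.0 cm with r = 0.7 implies a single-score SD of 3.0/√0.6 = 3.87 cm, which is doubtful on a 0–10 scale.

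Most of this stands as a limit on the claim: the loss is one of efficiency and of conditional bias, not of validity, and no single power gain should be quoted. It does not remove the point. The protocol itself names the primary tests, so this is a stated choice and not a detail left for later. The regression sentence cannot stand in for a primary model while its outcome, covariates and role are open. Nor does the endpoint require the t-test: a linear model with baseline VAS as covariate gives the same treatment coefficient whether the response is week-13 VAS or the change. ANCOVA had the higher power at every correlation and under both readings of the SD.

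**Conclusion.** The point holds. The primary comparison is unadjusted although baseline pain and the randomisation stratum are both in hand. With 3.0 cm as the SD of the change and 25 per group, power is 63.7% against about 71% to 82% with ANCOVA for r from 0.7 down to 0.3. With 3.0 cm as the SD of a single score, the gain runs from 18 points at r = 0.3 to 1.5 points at r = 0.8. These figures assume equal variances at the two visits and may be about one point too high for ANCOVA.

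Adjustment does not rescue the sample size. With 3.0 cm as the SD of the change, 80% power is reached only at r of about 0.3 or lower, and at none of the correlations examined once 10% are lost. The unreproduced 80% figure needs its own correction. This change should be made, but the trial would not be invalid without it.

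**What to change.** In Data analysis, name one primary model: a linear model of week-13 VAS on treatment arm, baseline VAS (continuous) and the randomisation age stratum (<50 or ≥50 years), reporting the adjusted mean difference in cm with its 95% confidence interval. Apply the same form to FIQ-R, sit-to-stand, EQ-5D and NRS-Anxiety, each with its own baseline. Move the unadjusted t-test and the Mann–Whitney test to supportive analyses, and state the role and covariates of any further multivariable regression.

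The cost is a sentence or two of text and two degrees of freedom (48 to 46), worth about 0.1 point of power. The model is standard in both SPSS and R and uses data already collected. The ethics section says nobody had been recruited at submission, and Protocol amendments gives the route for a change in analytical strategy. Fixing the model before any outcome data are seen also prevents a later choice between adjusted and unadjusted results.

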### Sample size

The sample size was calculated a priori to ensure both feasibility and statistical rigor. The calculation targeted the primary endpoint of pain intensity (VAS, 0–10 scale) from baseline to week 13. A minimal clinically important difference (MCID) of 2.0 cm and an expected standard deviation (SD) of 3.0 cm were assumed, based on previous randomized controlled trials in fibromyalgia populations evaluating pain reduction through behavioral and digital interventions [28,35]. Under these parameters, a total sample of 50 participants (25 per group) provides 80% power (two-tailed, α = 0.05) to detect a moderate-to-large effect size (Cohen’s d ≈ 0.65), using an independent t-test. The calculation was performed using G*Power software (version 3.1.9.6).

An attrition rate of approximately 10% was anticipated. Although higher dropout rates have been reported in some digital health trials, this estimate was considered reasonable given the structured follow-up, the short intervention period (13 weeks), and previous experience from our group showing high retention (>90%) in similar telehealth interventions for chronic pain. The sample size remains adequate after accounting for this expected loss. This calculation was finalised prior to recruitment to ensure prospective justification.

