### Multiplicity

As pain intensity (VAS) is the sole primary endpoint, secondary outcomes will be considered exploratory. No formal multiplicity adjustment will be applied; effect estimates will be reported with 95% confidence intervals to aid interpretation.

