Pre-specified subgroup analyses will explore treatment effects according to baseline pain severity (VAS ≥ 7 vs. < 7), age group (<50 vs. ≥ 50 years), and pharmacological treatment status (yes/no). Secondary outcomes will be considered exploratory. No formal multiplicity adjustment will be applied; effect estimates will be reported with 95% confidence intervals to support interpretation

All statistical tests will be two-tailed with α = 0.05. Analyses will be performed using IBM SPSS Statistics v28.0 and R software v4.3.2. Results will be presented with effect sizes, confidence intervals, and graphical summaries.

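### Two tests are named as the primary analysis of pain, each at 5%, with no rule for which one decides when they disagree

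*Protocol article*

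**What the plan says.** All of this is in the protocol article; no separate analysis plan is available.

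- **Data analysis**, in the paragraph that defines the primary analysis: change in VAS pain from baseline to week 13 is compared "between groups using both independent t-tests and Mann–Whitney U tests to ensure consistency of results".
- **Data analysis**, closing paragraph: "All statistical tests will be two-tailed with α = 0.05". Each of the two tests therefore has the full 5%.
- **Multiplicity**: "As pain intensity (VAS) is the sole primary endpoint, secondary outcomes will be considered exploratory", followed by "No formal multiplicity adjustment will be applied; effect estimates will be reported with 95% confidence intervals to aid interpretation". The reasoning concerns the number of endpoints. It does not address two tests of the same endpoint.
- **Sample size**: "A minimal clinically important difference (MCID) of 2.0 cm and an expected standard deviation (SD) of 3.0 cm were assumed", and the power statement is made "using an independent t-test". The Mann–Whitney test plays no part there.

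The same Data analysis section does give a rule for choosing between the two tests (Shapiro–Wilk), but only for comparing baseline characteristics. It also calls LOCF and complete-case analyses sensitivity analyses, a label it does not give to the Mann–Whitney test.

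**The concern.** A primary analysis should lead to one prespecified answer. Here there are two p-values for one endpoint, with no ranking and no rule for disagreement. Three rules are compatible with the text: the t-test decides, either test suffices, or both must be significant. They have different error rates and different power.

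The tests also ask different questions. The t-test concerns the difference in mean change in cm, which is the scale of the 2.0 cm target. The Mann–Whitney test concerns whether values in one arm tend to exceed those in the other, and it yields no mean difference. If they disagree, the trial report must choose between them. Without a written rule, that choice can follow the result.

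This is not a detail left for an analysis plan. The article itself fixes the primary analysis as both tests, so a plan naming only one would depart from it.

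**Working it through.** **Inputs from the protocol article.** 25 per arm, two-sided α = 0.05, target difference 2.0 cm, SD 3.0 cm (Sample size). Standardised difference d = 2.0/3.0 = 0.667; the article rounds this to about 0.65, so both values are used.

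**Step 1: the plan's own power figure.** The article states that "a total sample of 50 participants (25 per group) provides 80% power (two-tailed, α = 0.05". Exact noncentral-t power with 25 per arm is 61.5% at d = 0.65 and 63.7% at d = 0.667, so the stated 80% is not reproduced. That is a separate matter and not part of this point. Here the exact values serve to validate the simulation below.

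**Step 2: simulation.** 100,000 trials per scenario, 25 complete participants per arm, with the t-test and the asymptotic Mann–Whitney test run on the same data. The treatment effect is a pure shift of d standard deviations. The distributions are assumptions, because the article does not give the shape of VAS change: normal; strongly skewed (shifted exponential); heavy-tailed (t with 3 degrees of freedom, scaled to unit SD).

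Percentage of trials significant at 0.05:

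| Changes | d | t-test | Mann–Whitney | Either | Both | Disagree |
|---|---|---|---|---|---|---|
| Normal | 0 | 5.09 | 4.78 | 5.94 | 3.93 | 2.01 |
| Normal | 0.65 | 61.81 | 58.75 | 63.88 | 56.68 | 7.21 |
| Normal | 0.667 | 63.68 | 60.52 | 65.67 | 58.53 | 7.14 |
| Skewed | 0 | 4.65 | 4.71 | 6.56 | 2.80 | 3.76 |
| Skewed | 0.65 | 63.87 | 85.09 | 85.51 | 63.45 | 22.05 |
| Heavy-tailed | 0 | 4.69 | 4.78 | 6.35 | 3.12 | 3.24 |
| Heavy-tailed | 0.65 | 69.27 | 84.07 | 84.96 | 68.38 | 16.59 |

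**Step 3: internal checks.**

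- Either = t-test + Mann–Whitney − both. Normal, d = 0: 5.09 + 4.78 − 3.93 = 5.94.
- Disagree = either − both. Normal, d = 0.667: 65.67 − 58.53 = 7.14.
- Simulated t-test power (61.8% and 63.7%) matches the exact values in step 1.
- Monte Carlo standard error of the 5.94%: √(0.0594 × 0.9406 / 100,000) = 0.07 points. A separate run of 20,000 trials gave 5.8% for either and 3.9% for both. Its standard error is √(0.058 × 0.942 / 20,000) = 0.17 points, so the two runs agree.

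**Step 4: what the missing rule moves.**

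- Type I error with normal changes: about 5% with one designated test, 5.8% to 5.9% if either counts, 3.9% if both are needed.
- Power cost of needing both, normal changes: 63.68 − 58.53 = 5.15 points at d = 0.667; 61.81 − 56.68 = 5.13 points at d = 0.65.
- Conflicting verdicts at the planned effect: about 7% with normal changes, about 17% heavy-tailed, about 22% strongly skewed.

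**The case against.** The best defence is that the text already leans towards the t-test. The trial is sized on it, Cohen's d with a confidence interval is to be reported, and the stated purpose of running both tests is consistency, which can be read as a robustness check. That reading is reasonable, but the article never states it, and it does label other analyses as sensitivity analyses.

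It can also be said that the statistician stays blinded until database lock. This does not help: both p-values will be known once the analysis is run, and the rule is still missing then.

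A reader might infer several stronger things that the document does not support:

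- *The trial has no defined conclusion.* This holds only when the tests disagree. In the other 93% or so of trials (normal changes, planned effect) they give the same verdict.
- *The type I error is close to doubled.* Two independent tests would give 1 − 0.95² = 9.75%, but these two are highly correlated and the figure is about 6%. Even that applies only under an either-test rule, which the article does not adopt.
- *The mixed models and multivariable regression are further rival primary analyses.* Those sentences stand in the paragraph on secondary outcomes, and neither is called primary.
- *The no-adjustment statement is itself the error.* "No formal multiplicity adjustment will be applied" follows from treating secondary outcomes as exploratory. It simply does not reach this question.

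**Conclusion.** The point holds in a limited form. The article fixes the primary analysis as two tests, each at two-sided 0.05, and gives no hierarchy and no rule for disagreement. The principal harm is that the deciding test can be chosen after the results are seen.

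The effect on error rates is modest. Under normal changes the type I error lies between about 3.9% and 5.9% depending on the unstated rule, and requiring both tests costs about 5 points of power. The scope for discretion is larger: conflicting verdicts in about 7% of trials at the planned effect, and up to about 22% under strong skewness.

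These figures assume 25 complete participants per arm, a pure shift effect, and the distributions named above. The skewed and heavy-tailed cases are illustrative and have no source in the article. The point should be corrected, but it does not undermine the design.

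**What to change.** Name one decisive primary analysis of the between-group mean difference in VAS change, in cm, with estimates combined over the planned multiple imputations by Rubin's rules. Two choices would close the gap:

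- **Minimum:** the independent t-test, which matches the sample size calculation.
- **Preferable, but a separate gain:** the treatment coefficient from a linear model adjusted for baseline VAS and the age stratum used in randomisation. Both are already collected, and the article already lists baseline pain and age as covariates.

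Then add a sentence to this effect: the Mann–Whitney test on observed data is a sensitivity analysis and cannot change the primary conclusion.

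The cost is one or two sentences in Data analysis and no new data. The article reports that no participants had been recruited at submission. The change should be made before any unblinded results are seen, and recorded through the amendment route the article describes, because it alters the analytical strategy.
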